### 2.2.1 Secondary Outcome Measures

The secondary outcome measures collected at baseline, 12, 24 and 26 months are:

- i. *MDS-UPDRS total score* in the practically defined ON state – the total score consists of 65 items, where each item is scored between 0 (normal) and 4 (severe).
- ii. *MDS-UPDRS part II subscale score* in the practically defined ON state – the part II score consist of 13 items, where each item is scored between 0 (normal) and 4 (severe).
- iii. Timed motor tests:
  - a) *brain tap test* in the OFF state, where the measurement used is the number of key taps in 30 seconds,
  - b) *10 metre walk test (10MWT)* in the OFF state, which will consist of two components: number of 10MWTs the participant was able to complete out of three, and the mean time taken to successfully complete 10MWT.
- iv. *Montgomery and Asberg Depression Rating Scale (MADRS)* – a 10-item physician rated depression severity scale where each item is scored from 0 (best) to 6 (worst).
- v. *Addenbrooke's Cognitive Examination-III (ACE-III)* – total score which includes five subdomains: attention (score: 0-18), memory (score: 0-26), fluency (score: 0-14), language (score: 0-26) and visual spatial (score: 0-16).
- vi. *Non-Motor Symptom scale (NMSS)* – total score which comprises of 30 item rater-based instrument, specifically designed for the comprehensive assessment of non-motor symptoms in patients with PD. It contains nine dimensions: cardiovascular (2 items), sleep/fatigue (4 items), mood/cognition (6 items), perceptual problems (3 items), attention/memory (3 items), gastrointestinal (3 items), urinary (3 items), sexual function

- (2 items) and miscellaneous (4 items). Each item is scored for severity (0-3) and frequency (0-4).
- vii. *Parkinson's disease Questionnaire (PDQ-39)* total score – this questionnaire assesses how often people affected by Parkinson's experience difficulties. It consists of 39 items across eight discrete dimensions: mobility (10 items), activities of daily living (6 items), emotional well-being (6 items), stigma (4 items), social support (3 items), cognitions (4 items), communications (3 items) and bodily discomfort (3 items). Each item is scored between 0 (never) and 4 (always).
  - viii. *Levodopa-equivalent dose (LED)* – this measure allows for comparison of different types of PD medication by calculating the equivalent dose in Levodopa.

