| Total/HDL cholesterol ratio                                 |       | Safety of Simvastatin                                                                 |
| Incidents of diabetes at 24 months                          |       | Safety of Simvastatin                                                                 |
| LED                                                         |       | Distinguish symptomatic from disease modifying effects                                |
| Number of capsules every 6 months                           |       | Tolerability of simvastatin and trial protocol                                        |

Table 3: Secondary Outcomes and the objectives they will be used to assess.

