## APPENDIX

### A. ADDITIONAL INFORMATION FOR OUTCOME MEASURES

| PD Medication               | Conversion Factor |
|-----------------------------|-------------------|
| Amantadine                  | 1                 |
| Apomorphine                 | 10                |
| Azilect                     | 10                |
| Bromocriptine               | 10                |
| Cabergoline                 | 80                |
| Duodopa                     | 1.11              |
| Entacapone                  | 0.33*             |
| Levodopa dispersible        | 1                 |
| Levodopa immediate release  | 1                 |
| Levodopa controlled release | 0.75              |
| Lisuride                    | 100               |
| Madopar                     | 1                 |
| Mirapex                     | 100               |
| Opicapone                   | 0.5*              |
| Pergolide                   | 100               |
| Pramipexole                 | 100               |
| Rasagiline                  | 100               |
| Requip                      | 20                |
| Ropinirole                  | 20                |
| Rotigotine                  | 30                |
| Rytary                      | 0.6               |
| Safinamide                  | 100**             |
| Selegiline Oral             | 10                |
| Selegiline Sublingual       | 80                |
| Sinemet                     | 1                 |
| Sinemet controlled release  | 0.75              |
| Stalevo                     | 0.33*             |
| Tolcapone                   | 0.5*              |

\* Multiply immediate release levodopa dose by conversion factor and add to immediate release levodopa dose.

\*\* Add this value to the LED, regardless of dose.

Table 4: Conversion factors for levodopa-equivalent dose

Example: Immediate release Levodopa dose = 400 and Entacapone = 800, implies:

$$\text{LED} = (1 \times 400) + (0.33 \times 400) = 400 + 132 = 532$$

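### The COMT-inhibitor rule in Table 4 counts immediate release levodopa only, so regimens that the table rates as equal get different LED scores once the same inhibitor is added

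*SAP*

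**What the plan says.** SAP section 2.2.1 gives the purpose of LED: "this measure allows for comparison of different types of PD medication by calculating the equivalent dose in Levodopa". Table 3 in section 8.1 assigns it one objective: "Distinguish symptomatic from disease modifying effects". Under section 8.2 it is analysed, like the other continuous secondary outcomes, as a group difference at 24 months and in a repeated measures model.

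Section 4.6 derives LED by multiplying each drug's daily dose in mg by its Table 4 factor, and names two published sources for the factors. Table 4 in Appendix A gives immediate release levodopa a factor of 1, controlled release levodopa 0.75, Duodopa 1.11 and Rytary 0.6. Entacapone and Stalevo (0.33) and opicapone and tolcapone (0.5) carry an asterisk, and the footnote for that asterisk reads: "Multiply immediate release levodopa dose by conversion factor and add to immediate release levodopa dose".

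The one worked example has immediate release levodopa 400 and entacapone 800, and gives an LED of 532. The SAP does not say how an inhibitor taken with any other levodopa product is counted, and gives no reason for leaving those products out of the base.

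**The concern.** A conversion table exists so that regimens of equal dopaminergic strength get equal scores. Table 4 places controlled release levodopa on that scale at 0.75 per mg. The footnote then builds the inhibitor's contribution on immediate release levodopa alone, so the value of one inhibitor depends on which levodopa product it accompanies.

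Two consequences follow.

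- A participant who moves between formulations that the table treats as equivalent, while staying on the same inhibitor, is scored as having changed dopaminergic treatment.
- A participant on controlled release levodopa alone who starts an inhibitor is scored as having changed nothing.

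Both matter for an outcome whose stated use is to help separate symptomatic from disease modifying effects. The inclusion criteria (section 3.4.1) require wearing-off on dopaminergic treatment, and Table 4 itself lists inhibitors and several levodopa products that are not immediate release. The plan therefore provides for the combinations that the rule does not handle.

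**Working it through.** **Inputs**, all from Table 4 and its footnote: immediate release levodopa (IR) factor 1; controlled release levodopa (CR) factor 0.75; inhibitor factor f = 0.33 (entacapone) or 0.5 (opicapone, tolcapone).

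**Rule as written:** LED = IR + 0.75 × CR + f × IR.

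**Rule with the factor on all levodopa equivalents:** LED = (IR + 0.75 × CR) × (1 + f).

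**Step 1: reproduce the SAP's figure.** IR 400 with entacapone: 400 + 0.33 × 400 = 400 + 132 = 532. This matches.

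**Step 2: is there another operative rule?** The general rule in section 4.6 (mg × factor) applied to entacapone 800 mg gives 800 × 0.33 = 264, so the example would be 400 + 264 = 664. The SAP prints 532, so the footnote is the rule in force for these drugs.

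**Step 3: compare regimens that Table 4 rates as equal.** CR 400 / 0.75 = 533.3 mg has the same LED as IR 400 mg.

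| Inhibitor | IR 400 mg, as written | CR 533.3 mg, as written | Difference | CR 533.3 mg, factor on all levodopa equivalents |
|---|---|---|---|---|
| None | 400 | 400 | 0 | 400 |
| Entacapone (0.33) | 532 | 400 | -24.8% | 532 |
| Opicapone or tolcapone (0.5) | 600 | 400 | -33.3% | 600 |

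The differences are (400 - 532) / 532 = -24.8% and (400 - 600) / 600 = -33.3%. They come from the footnote alone, because the doses were chosen so that the 0.75 conversion cancels.

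**Step 4: starting an inhibitor on CR only.** CR 400 mg scores 0.75 × 400 = 300 before. As written it scores 300 + f × 0 = 300 after, for either factor.

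**Step 5: mixed regimens.** IR 200 mg plus CR 200 mg scores 200 + 150 = 350 without an inhibitor.

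- Entacapone: 350 + 0.33 × 200 = 416 as written, against 350 × 1.33 = 465.5.
- Factor 0.5: 350 + 0.5 × 200 = 450 as written, against 350 × 1.5 = 525.

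The discrepancy shrinks as the immediate release share grows.

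**Step 6: Stalevo.** Table 4 gives Stalevo its own row, but the footnote does not say which levodopa its factor multiplies. Take Sinemet 300 mg plus 300 mg of levodopa taken as Stalevo (an illustrative regimen).

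- Factor on Stalevo's levodopa only: 300 + 300 × 1.33 = 699.
- Factor on all immediate release levodopa: 600 × 1.33 = 798.

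The wording allows either reading.

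**The case against.** The strongest reply is that the footnote states a definite rule and the worked example follows it. The factors come from two cited papers that are not at hand, and those sources may restrict the increment to immediate release levodopa. If so, the SAP has copied its source correctly. This much stands: the documents do not show that LED is too low by a known amount for anyone on controlled release levodopa. A reader might infer that from the right-hand column of the table above, but those values come from one alternative rule and are not an established truth. The inconsistency within Table 4 does not depend on the sources, however. Regimens scored as equal become unequal when the same drug is added to both, which defeats the purpose given in section 2.2.1.

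Three other tempting readings go too far.

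- Moving from IR 400 mg to CR 400 mg on entacapone takes LED from 532 to 300, or -43.6%. That is not all due to the footnote. Table 4 intends a 25% drop at equal mg (400 to 300), and the footnote supplies the remaining factor of 400 / 532.
- The 33% or 50% is a share of the immediate release levodopa dose, not of total LED. If the regimen also included ropinirole 12 mg (assumed; 12 × 20 = 240), the increment would be 132 / 640 = 20.6% or 200 / 640 = 31.3%.
- Stalevo is not shown to be overcounted. Applied row by row, the footnote gives 699; the 798 needs the other reading. This is an ambiguity, not a demonstrated error.

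It is also fair to say that one rule applies to both arms of a blinded randomised trial, and that section 8.2 makes all secondary outcomes exploratory.

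**Conclusion.** The point holds as an inconsistent scoring rule of minor weight. Followed literally, the footnote gives a COMT inhibitor no value when levodopa comes only from controlled release products, Duodopa or Rytary. At doses that Table 4 rates as equal, this opens a gap of 24.8% (entacapone) or 33.3% (opicapone, tolcapone) in an individual's levodopa-related LED.

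The consequence is measurement error in one exploratory secondary outcome. A reader might infer a biased treatment comparison, but the SAP does not support that. It does not report how many participants take these combinations. With blinded, randomised allocation the error is mainly noise unless use of inhibitors or of non-immediate-release levodopa differs by arm. The primary futility analysis does not use LED.

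The conclusion assumes the literal reading of the footnote, since the SAP says nothing else on these combinations. It concerns how medication is scored, not how it is prescribed.

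**What to change.** 1. Check the footnote against the two conversion sources cited in section 4.6. If they restrict the increment to immediate release levodopa, say so in Appendix A and give the reason.
2. Otherwise, apply the entacapone, opicapone and tolcapone factors to the summed levodopa-equivalent dose: at minimum immediate release plus 0.75 × controlled release. State explicitly whether Duodopa and Rytary enter the sum, since the SAP offers no support either way.
3. State that Stalevo's factor applies only to the levodopa taken as Stalevo.
4. Add a worked example with controlled release levodopa.
5. The SAP's revision of 24 August 2020 was made with group allocations revealed. Label any re-derived LED as a post-unblinding correction, and report it beside LED derived by the footnote as it stands, with the number of participants in each arm whose value changes.

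The cost is one reworded footnote, a repeat of the LED derivation at all visits from medication data already held, and one extra set of LED results. No new data are needed.

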- LED – calculation of the LED will depend on the conversion factor, listed in Appendix A: Table 4, taken from Tomlinson, et al.  and Cervantes-Arriaga, et al. , where the daily dose in mg of the medication is multiplied by the conversion factor.

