## 8.2 SECONDARY OUTCOMES ANALYSIS

Continuous secondary outcome measures will be analysed:

- (i) at 24 months using mixed effects, linear regression models;
- (ii) across baseline, 12 and 24 months using repeated measures linear models.

Since incidence of diabetes is a binary measure only observed at 24 months, this secondary outcome will be modelled using a mixed effects logistic regression model.

The models will be adjusted by the covariates described in section 6.2, with the exception of the repeated measures models, which will not include the baseline measure as a covariate (as baseline data are included in the outcome being modelled).

As not all participants will be able to complete the 10MWT, the ability to complete the test, as well as the time, are both valuable indicators of PD progression. Therefore, we will analyse time and successful completion of the 10MWT as two components of this outcome measure.

We will model completing the 10MWT as:

- binary data – whether participant successfully completed at least one 10MWT (yes or no);
- continuous data - mean time, of participants who are able to complete at least one 10MWT.

The number of capsules and percentage of expected capsules returned every month will be reported for both of the allocated groups.

The secondary outcomes will not be tested under a futility hypothesis framework: allocated group differences will be assessed at the two-sided 5% level of significance and reported with two-sided 95% confidence intervals. As the trial is not powered to detect clinically meaningful differences on the secondary outcome measures, and no adjustments for multiplicity will be made, the results of the analyses of secondary outcomes will be interpreted and reported as exploratory only.

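### Table 4 gives Azilect a factor of 10 and rasagiline 100, so one drug at one dose yields two levodopa-equivalent doses

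*SAP*

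**What the plan says.** LED is one of the secondary outcomes in SAP section 2.2.1. Table 1 (section 4.5) shows it collected at baseline, 12, 24 and 26 months. Table 3 (section 8.1) gives its purpose as "Distinguish symptomatic from disease modifying effects". Sections 8.1 and 8.2 model continuous secondary outcomes at 24 months and across baseline, 12 and 24 months.

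Section 4.6 sends the derivation to Table 4 in Appendix A, "Table 4: Conversion factors for levodopa-equivalent dose", with the rule "where the daily dose in mg of the medication is multiplied by the conversion factor". Table 4 mixes brand and generic names. One row gives Azilect a factor of 10. Another reads "Rasagiline | 100".

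Two footnotes modify the multiplication rule. One covers entacapone, opicapone, Stalevo and tolcapone, whose factor is applied to the immediate-release levodopa dose. The other covers safinamide: "Add this value to the LED, regardless of dose". Neither footnote is attached to Azilect or rasagiline, so plain multiplication applies to both.

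**The concern.** Azilect and rasagiline are the brand and generic names of one substance, yet the table scores them ten-fold apart and the SAP gives no rule for mapping one name to the other. If an analyst takes the recorded name to the matching row, the LED depends on vocabulary as well as on treatment.

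Three consequences follow. Two participants on identical treatment can get different LEDs. One participant whose medication is written under different names at two visits shows a change in LED with no change in treatment. Even if naming is consistent within each participant, everyone scored on whichever row is wrong has that component mis-scored by a factor of ten. LED is meant to track how much symptomatic medication participants take, so false change in medication is the error that damages it most directly.

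**Working it through.** **Inputs.** From Table 4: Azilect 10, rasagiline 100. From section 4.6: contribution = daily dose in mg × factor. From the example under Table 4: LED of 532. The SAP gives no daily dose for this drug, so 0.5, 1 and 2 mg/day are assumed for illustration only.

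**Step 1. Reproduce the SAP's example.** Immediate-release levodopa 400 with entacapone: (1 × 400) + (0.33 × 400) = 400 + 132 = 532. This agrees with the SAP.

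**Step 2. Compare brand and generic rows in Table 4.**

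| Brand row | Factor | Corresponding row | Factor | Ratio |
|---|---|---|---|---|
| Mirapex | 100 | Pramipexole | 100 | 1 |
| Requip | 20 | Ropinirole | 20 | 1 |
| Sinemet | 1 | Levodopa immediate release | 1 | 1 |
| Madopar | 1 | Levodopa immediate release | 1 | 1 |
| Sinemet controlled release | 0.75 | Levodopa controlled release | 0.75 | 1 |
| Azilect | 10 | Rasagiline | 100 | 10 |

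**Step 3. Look for a legitimate reason for the split.** Table 4 does give one substance different factors by formulation, but then the row label says so: selegiline oral 10 and sublingual 80, levodopa immediate release 1 and controlled release 0.75. The Azilect and rasagiline rows have no such label and no footnote mark.

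**Step 4. Size of the gap.** Per mg of daily dose: 100 − 10 = 90 LED units. The last column is the gap divided by the total under the name Azilect.

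| Assumed dose (mg/day) | As Azilect | As rasagiline | Gap | Total on top of 532 | Gap as % |
|---|---|---|---|---|---|
| 0.5 | 5 | 50 | 45 | 537 or 582 | 8.4 |
| 1 | 10 | 100 | 90 | 542 or 632 | 16.6 |
| 2 | 20 | 200 | 180 | 552 or 732 | 32.6 |

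**Step 5. Effect on change over time, at 1 mg/day.** Constant treatment, recorded as Azilect at baseline and rasagiline at 24 months: 632 − 542 = +90 with no change in treatment. The reverse order gives −90. A participant who starts the drug after baseline shows a rise of 10 or of 100 according to the name used.

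**Step 6. Effect on a mean.** If a share p of all participants is scored on the wrong row at 1 mg/day, mean LED is displaced by p × 90. For an assumed p of 5% to 15% this is 0.05 × 90 = 4.5 to 0.15 × 90 = 13.5 units. The direction depends on which row is wrong, which the SAP does not settle.

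**The case against.** The strongest reply has four parts.

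First, the SAP never states that Azilect is rasagiline. That is true, but it is ordinary drug naming of the kind any medication coder must apply, and no outside conversion figure is needed to see the conflict.

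Second, a substance may properly have more than one factor, and the brand rows Duodopa (1.11) and Rytary (0.6) match no generic levodopa row. So the pattern in Table 4 is not by itself proof of an error. The case rests on the absence of any formulation label or footnote that would explain this particular split.

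Third, the discrepancy between visits arises only if names are scored as recorded. The SAP does not show the medication form or its coding, and no actual case of mixed naming is in evidence. This stands as a limit on what can be said about frequency. It does not remove the problem, because uniform naming would still apply one of two conflicting factors, and nothing in the SAP shows that it would be the right one.

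Fourth, the consequence is modest. Section 3.2 blinds participants, site teams and trial management, and section 4.1 stratifies randomisation by site, so naming habits should be roughly balanced between arms. Baseline adjustment in the 24-month models would absorb part of any consistent misnaming within a participant. LED does not enter the primary futility model or Equation 5, and section 8.2 says that "the results of the analyses of secondary outcomes will be interpreted and reported as exploratory only". All of this stands, and it limits the expected harm mainly to noise and mis-scored individual and descriptive values. Systematic bias between arms is unlikely, though chance imbalance is possible.

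**Conclusion.** The inconsistency is real. As written, Table 4 and section 4.6 give two LED values for the same treatment, exactly 90 units per mg of daily dose apart. That figure follows from the SAP and the identity of the two drug names. The percentages also rest on an assumed dose and on the SAP's worked example as the base, which need not be a typical participant's LED. The mean displacement of 4.5 to 13.5 units rests further on an assumed share of participants scored on the wrong row.

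The primary conclusion on futility is unaffected. The point should nevertheless be corrected, because following the table as printed can give a wrong value for a named secondary outcome and the remedy is small.

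**What to change.** Check both rows against the two sources cited in section 4.6, settle one factor, and apply it to both names. Add a sentence to section 4.6 or a note under Table 4 stating that brand names are mapped to the generic substance and formulation before scoring. With one factor f, the contribution is dose × f under either name and the naming gap is zero. Then rederive LED at baseline, 12, 24 and 26 months and run, or rerun, the LED summaries and models.

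The cost is one table cell, one sentence and a rerun of the derivation. No visit, treatment or model changes. The SAP revision of 24 August 2020 was made with group allocations revealed, so this correction should be dated and recorded as made after unblinding, with the factor chosen from the cited sources and not from the trial data. If LED results already exist, report how many participants' values change.

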## B. EXAMPLES OF FIGURES AND TABLES FOR REPORTING STUDY RESULTS

[figure not shown]

Figure 4: CONSORT Flow Diagram of participants through PD STAT.

|                                     | Simvastatin
N (%) | Placebo
N (%) | All
N (%) |
|-------------------------------------|----------------------|------------------|--------------|
| Age in years                 |                      |                  |              |
| Mean (SD) [range]                   |                      |                  |              |
| Median (IQR)                        |                      |                  |              |
| Female                       |                      |                  |              |
| Ethnic Origin                |                      |                  |              |
| White                               |                      |                  |              |
| Black Caribbean                     |                      |                  |              |
| Black African                       |                      |                  |              |
| Chinese                             |                      |                  |              |
| Indian                              |                      |                  |              |
| Pakistani                           |                      |                  |              |
| Bangladeshi                         |                      |                  |              |
| Other                               |                      |                  |              |
| Smoking Status               |                      |                  |              |
| Non smoker                          |                      |                  |              |
| Ex-smoker                           |                      |                  |              |
| Light Smoker                        |                      |                  |              |
| Moderate smoker                     |                      |                  |              |
| Heavy Smoker                        |                      |                  |              |
| Hoehn & Yahr             |                      |                  |              |
| 1.0                                 |                      |                  |              |
| 1.5                                 |                      |                  |              |
| 2.0                                 |                      |                  |              |
| 2.5                                 |                      |                  |              |
| 3.0                                 |                      |                  |              |
| Age in years at onset PD     |                      |                  |              |
| Mean (SD) [range]                   |                      |                  |              |
| Median (IQR)                        |                      |                  |              |
| < 30                                |                      |                  |              |
| 30 ≤ PD age < 40                    |                      |                  |              |
| 40 ≤ PD age < 50                    |                      |                  |              |
| 50 ≤ PD age < 60                    |                      |                  |              |
| 60 ≤ PD age                         |                      |                  |              |
| Disease duration             |                      |                  |              |
| Mean (SD) [range]                   |                      |                  |              |
| Median (IQR) [range]                |                      |                  |              |
| Diabetes Status at screening |                      |                  |              |
| None                                |                      |                  |              |
| Type 1                              |                      |                  |              |
| Type 2                              |                      |                  |              |

|                                   |  |  |  |
|-----------------------------------|--|--|--|
| Type 2 a               |  |  |  |
| Total Cholesterol (mmol/L) |  |  |  |
| Mean (SD) [range]                 |  |  |  |
| Median (IQR)                      |  |  |  |
| ≤ 5 mmol/L                        |  |  |  |
| > 5 mmol/L                        |  |  |  |
| QRISK® 2        |  |  |  |
| Mean (SD)                  |  |  |  |
| < 10%                             |  |  |  |
| ≥ 10%                             |  |  |  |
| QRISK® 2        |  |  |  |
| Median (IQR) [range]              |  |  |  |
| < 10%                             |  |  |  |
| ≥ 10%                             |  |  |  |
| MoCA                       |  |  |  |
| Mean (SD) [range]                 |  |  |  |
| Median (IQR)                      |  |  |  |
| MADRS                      |  |  |  |
| Mean (SD) [range]                 |  |  |  |
| Median (IQR)                      |  |  |  |
| AST                        |  |  |  |
| Mean (SD) [range]                 |  |  |  |
| Median (IQR)                      |  |  |  |
| ALT                        |  |  |  |
| Mean (SD) [range]                 |  |  |  |
| Median (IQR)                      |  |  |  |
| CK                         |  |  |  |
| Mean (SD) [range]                 |  |  |  |
| Median (IQR)                      |  |  |  |

Table 7: Baseline and Demographic Data

|                      | Mean (SD) | Fully Adjusted*      |         | Adjusted Only for Baseline MDS-UPDRS Part III Score |         |
|----------------------|-----------|----------------------|---------|-----------------------------------------------------|---------|
|                      |           | Coeff. Est. (80% CI) | p-value | Coeff. Est. (80% CI)                                | p-value |
| Primary analysis     |           |                      |         |                                                     |         |
| Placebo              |           |                      |         |                                                     |         |
| Simvastatin          |           |                      |         |                                                     |         |
| Sensitivity Analysis |           |                      |         |                                                     |         |
| Placebo              |           |                      |         |                                                     |         |
| Simvastatin          |           |                      |         |                                                     |         |

\* The analysis is adjusted for baseline MDS-UPDRS part III, recruiting site, modified Hoehn & Yahr score, disease duration, gender and age at baseline.

Table 8: Primary outcome analysis: linear regression of change in MDS-UPDRS score part III at 24 months in the OFF state.

| Secondary Outcomes       | State | Fully Adjusted* (95% CI) |          | Adjusted Only for Baseline Score (95% CI) |          |
|--------------------------|-------|--------------------------|----------|-------------------------------------------|----------|
|                          |       | 24 months                | Repeated | 24 months                                 | Repeated |
| MDS-UPDRS         |       |                          |          |                                           |          |
| Part II                  | ON    |                          |          |                                           |          |
| Total                    | ON    |                          |          |                                           |          |
| Timed Motor Tests |       |                          |          |                                           |          |
| Brain tap test           | OFF   |                          |          |                                           |          |
| Walk test                | OFF   |                          |          |                                           |          |
| Questionnaire     |       |                          |          |                                           |          |
| MADRS                    | ON    |                          |          |                                           |          |
| ACE-III                  | ON    |                          |          |                                           |          |
| NMSS                     | ON    |                          |          |                                           |          |
| PDQ-39                   | ON    |                          |          |                                           |          |
| KPPS                     | ON    |                          |          |                                           |          |
| Cholesterol       |       |                          |          |                                           |          |
| Total                    | NA    |                          |          |                                           |          |
| HDL                      | NA    |                          |          |                                           |          |
| Total/HDL ratio          | NA    |                          |          |                                           |          |
| Diabetes          | NA    |                          |          |                                           |          |
| LED               | NA    |                          |          |                                           |          |

EMS - electromagnetic sensor; MADRS - Montgomery and Asberg Depression Rating Scale; ACE-III - The Addenbrooke's Cognitive Assessment-III (ACE-III); NMSS - Non-Motor Symptom assessment scale (NMSS); PDQ-39 - Parkinson's disease Questionnaire (PDQ-39); LED - levodopa-equivalent dose; KPPS - King's PD pain scale; EQ-5D-5L - EuroQoL 5D-5L health status questionnaire.

\* Differences are adjusted for outcome measure at baseline (where available), recruiting site and modified Hoehn & Yahr score, disease duration, gender and age at baseline.

Table 9: Differences between placebo and intervention group (i.e. placebo – intervention) with corresponding 95% confidence intervals for all secondary outcomes.

